### Assessments

In this study, we will assess parents, children, and teachers. The assessments were taken before (T1 = one week before intervention), after (T2 = one week after intervention), and follow-up the interventions (T3: six weeks after intervention). To reduce recall bias for health data, we will also combine children’s electronic medical records. The research tools are shown in Table 2. We will use measurement instruments that are well-validated and reliable instruments. The control variables mainly include children’s, parental and teacher’s socio-demographic characteristics. Moderator and mediator variables include children’s resilience, coping methods, family environment, school environment, etc.

**Table 2 Tab2:** Assessment tools

Category	Variables	Indicator/tools	Data sources
**Outcomes**	PTSS	PTSD Checklist for DSM-5 (PCL-5)	Parents/Child
	Depression	10 Items The Center for Epidemiological Studies-Depression (CESD-10), The Strengths and Difficulties Questionnaire (SDQ)	Child
	Anxiety	Self-Rating Anxiety Scale (SAS)	Child
	Bullying	Delaware bullying victimization scale	Child
**Predictors**	Trauma event	PCL-5 checklist	Child
	Intervention related	Participate, Stratification	Child/teacher
**Confounding**	Child characteristics	Gender, age et al.	Child
	Parent characteristics	Gender, age, marital status et al.	Parent
	Teacher characteristics	Gender, age, teaching background et al.	Teacher
**Moderator/Mediator**	Resilience	14-Item Resilience Scale (RS-14)	Child
	Coping style	Simplified Coping Styles	Child
	Family environment	Family Functioning Style Scale	Child
	School environment	Delaware School Climate scale	Child

### Project activities

Taking advantage of ongoing monitoring and evaluation of the quality of intervention and continuous data collection in the program, this study will achieve the goals and objectives through the following tasks and approaches.

## 1. Design of supportive environment

Initially, our study will contact professional psychology teachers, social workers, head teachers and administrative staff in selected counties and establish long-term partnerships, in order to build a supportive environment supporting conduction of research and protecting child mental health.

## 2. Pilot trails and screening

Before the beginning of the formal study, pilot trails will be conducted to estimate the feasibility of a large RCT of School-based Psychosocial Interventions and improve its detailed design, in the first half-year of 2023. Main task in the second half of 2023 is collecting baseline data before the intervention. Baseline data including basic information (i.e. age, gender) and mental health status of children, their parents and teachers will be assessed via questionnaire surveys. And the core of screening is identifying children’s priority trauma mental health problem and its key roles.

## 3. Trauma recognition and treatment intervention

Intervention will be conducted from the January to December in 2024. The lectures related to mental health will be provided to parents and their children and improve their trauma cognition by school psychology teachers. Next a series of courses and activities will carry out to improve stress coping skills among children. For parent-child sessions, this study will use qualitative interviews methods and hold child-parents trauma narrative discussion to improve effective parent-child communication, reinforcing cognition training.

## 4. Evaluation of intervention and development of recommendations

To evaluate the effectiveness and implementation of the intervention and build a safe school environment for children mental health, our study will collect follow-up data from July 2024 to December 2025, and conduct an effectiveness-implementation study to evaluate the satisfaction and effects of the intervention. Lastly, researchers will write corresponding report and make a school-based health program targeted to physical and mental health of parents and their children.

## 5. Baseline and follow-up questionnaire survey

Questionnaire survey data will be collected by dedicated regional coordinators, graduate students, and undergraduate students. The assessments will be conducted in each cluster at baseline, at the start of the trial, and at subsequent 6-week intervals until the trial ends. All interviewers will receive 2 days of professional training. The training content includes the explanation of the questionnaire, filling instructions and caveats. Prior to the start of the study, each interviewer will conduct a half-day trial interview. According to the trial visit, potential problems appearing in investigation process are explained in a unified manner. All the children, their parents and the school teachers were informed the purpose of this study and signed the informed consent form.

### Statistical methods

All analyses are on an intention-to-treat basis, with all randomized participants included in the analysis and analyzed according to original group assignment regardless of treatment dose received. Descriptive statistics will be used to summarize the characteristics of the participants. Generalized linear mixed models (GLMMs) will be used to evaluate the effectiveness of the intervention on outcomes using a three-level multilevel model. This model includes intervention status, time, and the treatment between intervention and time as fixed effects. Dependency in the repeated measurements within individuals will be modeled using a random intercept and random slope at the participant level. A random intercept at the school level will be used to model dependencies between children within the same school. The interaction between treatment and schools will also be tested to investigate the cluster effects. Confounders will also be included as fixed effects in the model, including gender, age, parent characteristics, and teacher characteristics. The estimated intervention effect will be reported as the mean outcome differences (at T2, T3) and 95% confidence interval (95% CI) between the intervention and control groups. All covariate-by-condition interactions on child mental health will be examined.

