**Methods:**

This study will conduct a cluster randomized controlled trial (RCT) in a large sample of Chinese rural children. Four rural counties in Shandong (Central China), Henan (Central China), Inner Mongolia (Northern China), and Xinjiang (Western China) will be selected as study settings from which schools will be sampled. Each sampled school will be randomly allocated either the intervention groups or a control group. Randomization will be performed by the research member who is not involved in the intervention stage. In each school students in grade 5 or higher will be recruited to ensure that approximately 50 children aged 10 to 18 years will be included. In each county, one high school, one middle school, and one primary school will be randomly chosen as the intervention group, and the other three similar schools will be chosen as control (waiting list) groups. A standardized and uniform research protocol will be applied in all intervention schools. All school social workers and psychological teachers would receive one week of in-person training following procedures. School-based psychosocial interventions included 14 group sessions for 14 consecutive weeks.

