## Methods

### Study design and randomization

As shown in Fig. 1, this study is a multicenter cluster randomized controlled trial. School as the study unit will be randomly assigned to the intervention or the control group. Four rural counties in Shandong (Central China), Henan (Central China), Inner Mongolia (Northern China), and Xinjiang (Western China) will be selected as study settings. These counties were selected due to their vulnerability in socioeconomic development and weakness of the mental health system. In addition, we have good cooperation with the local schools in these areas, which ensure a high participation rate. The schools were randomly allocated to either the intervention or control group using a random number generator. Randomization will be performed by the research member who is not involved in the intervention stage. Grade 5 above in each school will be recruited to ensure that approximately 50 children aged 10 to 18 years are included. After being informed about the survey’s aims, children will be asked to provide informed consent and informed that they can join the study voluntarily. Informed consent also will be obtained from their parents/legally authorized representatives.

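### The model lets change over time vary by child but not by school, so the standard error of the treatment-by-time contrast is too small if schools differ in change; the planned treatment-by-school test does not address this

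*Protocol article*

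**What the plan says.** Under Study design and randomization, the protocol article makes the school the unit of allocation: "School as the study unit will be randomly assigned to the intervention or the control group". The Methods part of the Abstract gives the layout: "In each county, one high school, one middle school, and one primary school will be randomly chosen as the intervention group", with three similar schools as controls. Each school therefore has one condition only.

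Statistical methods fixes the model. For the fixed effects: "This model includes intervention status, time, and the treatment between intervention and time as fixed effects" (the last term can only be the intervention-by-time interaction). For the child: "Dependency in the repeated measurements within individuals will be modeled using a random intercept and random slope at the participant level". For the school: "A random intercept at the school level will be used to model dependencies between children within the same school". No school slope or school-by-time term is named. One further step on clustering is planned: "The interaction between treatment and schools will also be tested to investigate the cluster effects".

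On the reported effect: "The estimated intervention effect will be reported as the mean outcome differences (at T2, T3") with a 95% confidence interval. The Assessments section sets three measurement times, a baseline and two after the intervention: "The assessments were taken before (T1 = one week before intervention), after (T2 = one week after intervention"), followed by T3.

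**The concern.** The random-effects structure recognises that children change at different rates, but assumes that all schools in an arm share the same average change. A school intercept is the same at T1, T2 and T3, so it drops out when change is compared between arms. Any real difference between schools in change is then attributed to children as if they were independent, and 40 children from one school count as nearly 40 separate pieces of evidence about change.

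The article gives reasons to expect such differences. Aims and hypotheses proposes that social workers, headteachers and the school environment alter the effect. Interventions has staff of each school leading the groups and plans to examine effects at social-worker level. At stake is the validity of the test and of the confidence interval for the difference in change: a false positive would be more likely than the 5% level suggests.

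**Working it through.** **Inputs from the article (Sample sizes and subjects; Abstract).** 4 counties x 6 schools = 24 schools, 12 per arm; 50 children per school; ICC 0.05; attrition 20%, so m = 50 x 0.8 = 40 followed per school; 5% significance, taken as two-sided. The article states no standard error or error rate for this contrast, so there is no figure of its own to reproduce.

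**Assumptions, because the article is silent.** The correlation of a school's effect over time (CAC) is varied from 1.0 down to 0.8. The child-level correlation over time (r) is 0.5 or 0.7. The outcome has SD 1.

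**Formulas for the difference in mean change from T1 to one later time.**

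- Between-school variance of change: Vb = 2 x 0.05 x (1 - CAC)
- Within-school variance of change: Vw = 2 x 0.95 x (1 - r)
- Squared SE with a school intercept only: 2(Vb + Vw)/(12m)
- Correct squared SE: 2(Vb/12 + Vw/(12m))
- Type I error: 2 x [1 - Phi(1.96/ratio)], where ratio = correct SE / intercept-only SE

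**One case in full (CAC 0.9, r 0.5).** Vb = 0.01 and Vw = 0.95. Intercept-only: 2 x 0.96/480 = 0.00400, SE 0.063. Correct: 2 x (0.01/12 + 0.95/480) = 0.00563, SE 0.075. Ratio 1.19; 1.96/1.19 = 1.65; type I error 9.8%.

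| CAC | r | SE, intercept only | SE, correct | Ratio | Type I error |
|---|---|---|---|---|---|
| 1.0 | 0.5 | 0.063 | 0.063 | 1.00 | 5.0% |
| 1.0 | 0.7 | 0.049 | 0.049 | 1.00 | 5.0% |
| 0.9 | 0.5 | 0.063 | 0.075 | 1.19 | 9.8% |
| 0.9 | 0.7 | 0.049 | 0.064 | 1.29 | 13.0% |
| 0.8 | 0.5 | 0.064 | 0.085 | 1.34 | 14.5% |
| 0.8 | 0.7 | 0.050 | 0.076 | 1.52 | 19.8% |

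**Simulation of the stated model under no effect** (r = 0.5, 24 schools, 40 children, three times, 600 runs per setting; Monte Carlo standard error near 5% is about sqrt(0.05 x 0.95/600) = 0.9 points). Rejection rates for the change contrast, T2/T3:

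| CAC | Stated model, z | Plus school slope, z | Plus school slope, t on 22 df |
|---|---|---|---|
| 1.0 | 5.8% / 5.5% | 5.2% / 4.5% | 3.7% / 3.0% |
| 0.9 | 8.2% / 10.3% | 6.3% / 4.8% | 5.3% / 4.3% |
| 0.8 | 14.2% / 14.3% | 7.3% / 5.7% | 4.8% / 4.5% |

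The simulation agrees with the closed form. At CAC 0.8, keeping the stated random effects and only changing the reference to t on 22 df leaves 11.3% / 12.7%, so most of the correction comes from the school-level term. A linear school slope is not always enough: at CAC 0.6 it still left 7.5% at T2 by t. A school-by-time effect is therefore the safer form.

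**Plain arm difference at T2 or T3.** Here the school intercept does not cancel. The same simulation, over CAC 1.0 to 0.6, gave 5.5-7.7% by z and 4.0-6.7% by t. A separate simulation with r of 0.5-0.7 and CAC of 0.7-0.95 gave about 6-9%.

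**Treatment by school.** No school is seen under both conditions. As a fixed effect the interaction is aliased with the school effects and cannot be estimated. As a random term it lets the school intercept variance differ between arms. That variance is still constant over time and still cancels from the change contrast.

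**The case against.** The strongest reply is that the reported effect, read literally, is the arm difference at each of T2 and T3, for which the stated model is close to nominal. This stands as far as it goes. But the article does not say whether it means a level difference or a difference in change, the model contains the interaction, and Aims and hypotheses speaks of symptoms decreasing in intervention schools and not in control schools, which is a comparison of changes.

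It is also true that the inflation is conditional. If schools keep their relative positions exactly (CAC 1.0), the standard error is right, and the article gives nothing from which to estimate CAC or r.

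Two stronger inferences are tempting and not supported. A reader might say that differing school trends bias the effect estimate. They do not: schools are randomised, so the trends add variance that the model leaves out. A reader might also blame the treatment-by-school test for the small standard error. The cause is the missing school-by-time term; the test merely fails to reveal or cure it. Nor is that test impossible on every reading: it can be fitted as a random term, or perhaps as an interaction with school type, which the text does not say. Neither reading helps the change contrast.

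Finally, the choice of small-sample degrees of freedom commonly belongs in an analysis plan, and its absence here is not a fault. The random effects, however, are stated explicitly in the article.

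**Conclusion.** The model as written leaves out between-school variation in change, at the level where the trial randomises and treats. If schools differ in change, the standard error of the treatment-by-time contrast is too small, by a factor of 1.19-1.29 at CAC 0.9 and 1.34-1.52 at CAC 0.8. This rests on the article's ICC of 0.05, 40 children followed per school and an assumed r of 0.5-0.7. A reader might infer that the trial's test will certainly reject far more often than 5%. The documents do not support that, because neither correlation is given and the contrast to be reported is not settled. The specification still needs correcting, because it is sound for the change contrast only if schools do not differ in change at all, and the plan's one further check on clustering cannot show whether that is so.

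**What to change.** In Statistical methods:

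- Keep the school random intercept and add a random school-by-time effect, or use a school-level covariance matrix over T1-T3. Use small-sample degrees of freedom suited to 24 schools (Kenward-Roger or Satterthwaite; about 24 - 2 = 22 before school-level covariates).
- State whether the effect at T2 and T3 is a difference in level or a difference in change from T1.
- Replace the treatment-by-school test with treatment by county and treatment by school type. Both are estimable because each county (3 against 3 schools) and each school type (4 against 4) contains both arms. With so few schools per cell these tests are exploratory, and they do not replace the school-by-time term.

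The cost is analysis wording only, with no change to design or data collection. Intervals for the change contrast widen by the ratios above where schools do differ. With r = 0.5, power to detect a difference in change of 0.20 on 22 df is 0.87 at CAC 1.0, 0.72 at 0.9 and 0.61 at 0.8. That loss is inherent in the design, and the stated model only hides it.

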### Sample sizes and subjects

The required sample size to detect an expected intervention effect with sufficient statistical power was calculated for the primary outcome posttraumatic stress symptoms, as measured with the PTSD Checklist for DSM-5 (PCL-5) scale, using a method that considers the estimation of effect size, repeated measurements, significance level, power, allocation ratio, and attrition rate at T2, and T3. The following parameters are used: (1) the effect size estimations for the primary outcome is 0.20 (based on a meta-analysis [33]); (2) the intraclass correlation is 0.05; 4) 5% level of significance; 5) 80% level of power; 6) allocation ratio of 1:1; and 7) attrition rate of 20%. Under these hypotheses, we expect a sample size of at least 24 clusters (i.e., schools) with 50 children in each school to be included, resulting in a total intended sample size of 1200 children, 1200 parents and 30 teachers. The sample size will be distributed as evenly as possible among the control schools and intervention schools.

Eligibility criteria: As school is our intervention unit, the inclusion criterion is that the school should not have a similar psychosocial intervention program. For students, all children in the program schools who have signed informed consent will participate in this program. Exclusion criteria: Children with severe physical and mental health problem, and unable to participate into the program completely.

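### Schools are balanced by county and school type and PCL-5 is measured at T1, but the primary model names neither allocation factor and the reported T2 and T3 differences are not adjusted for chance T1 imbalance

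*Protocol article*

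**What the plan says.** **Allocation.** The Abstract (Methods) says "In each county, one high school, one middle school, and one primary school will be randomly chosen as the intervention group", and that "the other three similar schools will be chosen as control (waiting list) groups". Reading similar as same type, four counties, three school types and two arms give 24 schools in 12 cells, with one school per arm in each. The Methods section, under Study design and randomization, says only "The schools were randomly allocated to either the intervention or control group using a random number generator" and mentions neither county nor school type.

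**Model.** Statistical methods specifies a three-level mixed model. Its fixed effects are intervention status, time and their interaction. It has a participant random intercept and slope and a school random intercept. On covariates it says "Confounders will also be included as fixed effects in the model, including gender, age, parent characteristics, and teacher characteristics".

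**Reported effect.** "The estimated intervention effect will be reported as the mean outcome differences (at T2, T3) and 95% confidence interval" between the two arms. The text does not say that these differences are relative to T1, that the arms are constrained to be equal at T1, or that T1 PCL-5 is a covariate.

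**The concern.** Two sources of removable noise appear to stay in the primary estimate.

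1. **Allocation factors.** If PCL-5 differs between counties or school types, the allocation balances that variation across arms. A model without those terms still counts it as error. The standard error is then too large and the test conservative.

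2. **Baseline.** When intervention status and its interaction with time are both free, time is categorical and data are complete, the fitted arm difference at T2 is the T2 post-test difference, apart from the listed covariates. Having T1 as an outcome row does not change that. Only a constraint at T1, or T1 as a covariate, transfers the baseline information to the T2 and T3 contrasts.

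With only 12 schools per arm, chance differences between arms at T1 can be large relative to the effect sought, so the handling of T1 matters for precision and for how the result reads.

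**Working it through.** **Inputs from Sample sizes and subjects.** "the effect size estimations for the primary outcome is 0.20" (taken as standardised, SD = 1); "the intraclass correlation is 0.05"; "5% level of significance" (two-sided assumed); 80% power; 20% attrition; 24 schools of 50, so 40 completers per school and 12 schools per arm.

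**The plan's own figure.** 393 children per arm without clustering; design effect 1 + 49 × 0.05 = 3.45; total 2 × 393 × 3.45 = 2,712, or 2,712 / 0.8 = 3,390 with attrition. The stated 1,200 is not reproduced. That is a separate matter, but it means precision is scarce.

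**Post-only difference, no county or type.** V = (2/12)(0.05 + 0.95/40) = (2/12)(0.07375) = 0.01229, so SE = 0.111. Power at 0.20 (noncentral t, 22 df) is 41%.

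**Chance T1 difference.** All 50 children per school are measured, and s is the share of between-school variance due to county and type, which the allocation balances:

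SD = √[(2/12)(0.05(1 − s) + 0.95/50)]

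- s = 0: √0.0115 = 0.107
- s = 0.3: √0.0090 = 0.095
- s = 0.5: √0.00733 = 0.086

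**T1 adjustment.** The protocol gives no baseline correlation, so a range is assumed. The correlation of school means between T1 and follow-up is r = (0.05 × school correlation + 0.95 × child correlation / 40) / 0.07375. The covariate-adjusted variance is V(1 − r²), and the change-from-T1 variance is 2V(1 − r).

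| School / child correlation | r | SE and power, T1 covariate | SE and power, change from T1 |
|---|---|---|---|
| 0.3 / 0.3 | 0.30 | 0.106, 44% | 0.131, 31% |
| 0.5 / 0.5 | 0.50 | 0.096, 51% | 0.111, 41% |
| 0.7 / 0.5 | 0.64 | 0.086, 61% | 0.095, 52% |
| 0.7 / 0.7 | 0.70 | 0.079, 68% | 0.086, 61% |
| 0.8 / 0.6 | 0.74 | 0.075, 72% | 0.081, 66% |

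T1 adjustment beats the change contrast in every row, and the post-only 41% as well.

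**County and school type.** School means were simulated under the 12-cell allocation, with 40 completers per school and the share s split equally between county and type. The adjusted model spends 3 + 2 = 5 df.

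| s | Power without → with | Type I error without the terms |
|---|---|---|
| 0% | 41% → 40% | about 5% |
| 30% | 42% → 48% | about 3.5% |
| 50% | 43% → 55% | about 2.3% |

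The type I rates at 30% and 50% move by up to about one percentage point with how the county and type effects are simulated, but stay below 5%. With the terms included, the rate is close to 5%.

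**Both together.** At s = 0.3 and r = 0.5: V = (2/12)(0.05 × 0.7 × 0.75 + 0.95 × 0.75/40) = 0.00734, SE 0.086, power about 60%.

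**Teacher characteristics.** About 30 teachers over 24 schools is 1.25 per school, so these covariates are nearly school-level. Table 2 lists at least three. Three uninformative ones, simulated, take power from 41% to 36% without county and type, and from 55% to 47% with them at s = 0.5.

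**The case against.** Much can be said for the plan.

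- **T1 is in the model.** It is one of three repeated outcomes, and the interaction terms carry change from T1. A reader might infer that baseline PCL-5 is ignored altogether; the documents do not support that. The reported differences could also be meant as change-from-T1 contrasts. That reading shrinks the gain (for example 52% to 61%, or 66% to 72%) but does not remove it.
- **The covariate list is open.** It is introduced by a word that allows further terms, and a fuller analysis plan could add county and type. It remains odd to name teacher characteristics and not the factors used in allocation.
- **Age is already a covariate.** Primary, middle and high schools largely divide the 10-18 age range, so the net gain from school type is smaller than shown. Age captures nothing of county.
- **The gains are assumed.** Neither the correlations nor the 30-50% share comes from the protocol. At a 0% share the county and type terms cost about one point of power.
- **No loss of validity.** A reader might infer an invalid test from the omitted factors. The error is conservative.
- **Teacher and parent covariates.** A reader might infer that teacher terms waste precision, or that children with missing parent data are dropped. The first holds only if the terms are not prognostic. The second holds only under complete-case fitting, which the protocol does not state; it promises to include all randomised participants.

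**Conclusion.** The point holds in a limited form. The allocation described in the Abstract is balanced on county and school type, and neither factor is named in the model or in the Methods account of randomisation. The T2 and T3 differences, as the model is written, are not adjusted for chance T1 imbalance, whose SD is 0.086 to 0.107 depending on how much of the between-school variance the allocation balances; that is roughly half the 0.20 target.

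The direction of the T1 gain is secure over the whole range tried, but its size depends on correlations the protocol does not give. The gain from county and type depends on their share of the variance and is partly pre-empted by age. The consequence is lost precision and a somewhat conservative test, not bias in expectation or an inflated error rate. The change is worth making because it is cheap and uses data already planned.

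**What to change.** 1. In the primary model, either constrain the arms to be equal at T1 (drop the intervention main effect and keep arm × T2 and arm × T3) or use T1 PCL-5 as a covariate for T2 and T3. State that the reported differences come from those terms.
2. Add county (3 df) and school type (2 df) as fixed effects, alongside child age and gender.
3. In Study design and randomization, state that allocation is within county and school type, so that it agrees with the Abstract.
4. Optionally, move teacher characteristics to a sensitivity analysis, or give a reason to expect them to be prognostic.

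Cost: wording, and 5 of about 22 school-level degrees of freedom. No new data are needed.
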